## Abstract

Long-term breast cancer survivors (>5 years free of disease) may suffer late sequelae of cancer that impact on their quality of life. The use of telehealth for cancer care is recommended but little is known about the effectiveness of digital interventions for long-term cancer survivors. This study aims to evaluate the effectiveness of a web-based personalized intervention based on artificial intelligence instead of usual primary health care to improve the quality of life of long-term survivors of breast cancer and self-efficacy for the management of late sequelae. A randomized controlled trial will be conducted. The sample will consist of long-term breast cancer survivors recruited from primary health centers. Women will be randomly assigned to the intervention group to receive a web-based personalized intervention or to the control group to receive standard primary health care by nurses. Data on quality of life of cancer survivors and self-efficacy for the management of late sequelae of cancer will be collected and assessed at preintervention, and at 3, 6, and 9 months. It is expected that, at the end of the programme, the experimental group will have improved quality of life and improved self-efficacy for the management of late sequelae of cancer.

## 1. Introduction

The cancer survivor population is growing. Early detection, therapeutic and pharmacological advances, and greater access to health services have influenced this increase in breast cancer survival [1]. The epidemiological data of the EUROCARE project on the survival of cancer patients in Europe show the change in the course of cancer, which has gone from being an acute terminal disease to a chronic process of long duration [2]. In the case of breast cancer, overall survival at 5 years after diagnosis is one of the highest in Europe [3]. The approach to cancer has also undergone significant changes in the past 25 years, achieving prolonged survival due to the improvement of treatments and care, including surveillance of recurrence and second tumors and control of symptoms and psychosocial needs. In Spain, breast cancer survival has increased from 67.5% years in 1985–1989 to 83.7% in 2010–2012, and net survival rates at 5 years are 96.6% for patients with tumors diagnosed in stage I, 88.2% for stage II, 62.5% for stage III, and 23.3% for stage IV [4].

Classically, three stages of cancer survival are distinguished [5]: acute survival (living with cancer), extended survival or intermediate survival (disease remission and monitoring of the process during the first 3–5 years), and permanent survival or long-term survival, also known as the healing and coexistence phase after cancer. Studies carried out with long-term survivors (LS) show that patients may have physical and psychosocial needs, which are often not covered by the health system [6]. Therefore, it is precisely in the stage of long survival where greater co-ordination and health continuity are needed to address the specific needs, problems, and challenges faced by LS and, in particular, long-term survivors of breast cancer (LS-BC) [7].

Currently, an area of special national and international interest focuses on the care of LS with a greater participation of primary care providers and greater continuity and co-ordination between specialized care in oncology and primary health care (PHC) [8,9]. It has been shown that shared care between oncology specialists and primary care professionals can be effective and profitable and that primary care nurses can play a relevant role in the optimization of education and promotion of health among survivors [10,11]. Likewise, patients value accessibility to health services, continuity and co-ordination of care—fundamental pillars of PHC—and show greater satisfaction when receiving individualized care focused on their needs [10].

In this context, the following care practices are recommended in the follow-up of LS-BC by primary care professionals: promotion of healthy lifestyles, personalized counselling and education for self-management of sequelae derived from treatments and care for the cancer and its symptoms (lymphedema, fatigue, pain, adverse cardiovascular events, musculoskeletal symptoms, accelerated bone loss and fractures, skin changes due to radiation, chemo brain, anxiety, depression, fear of recurrence, post-traumatic stress, altered interpersonal relationships, problems with sexuality and reproduction, altered body image, emotional, and social and work adaptation), prevention of relapses, and emotional and family support [10,12]. All of these recommendations are made with the objective of improving the living experience of the chronic process of cancer, achieving higher levels of quality of life in survivors and optimizing care resources [13,14].

However, although in the international context there are successful implementation experiences in PHC of cancer survivorship care plans [13], in Europe, and, in particular, in Spain, this implementation is moving slowly [15]. In addition, the role of the primary care team in providing care for long-term cancer survivors is not clearly defined, and few programmes have been implemented to improve care activities, standardized protocols, develop documentation and records, or update training of professionals [16,17]. Therefore, organizational and care changes are needed, favoring the implementation of structures for collaboration and shared decision making that produce greater autonomy for cancer survivors and their families.

It is key to consider the health context that surrounds us to implement health activities and programmes that are cost-effective and sustainable. The COVID−19 pandemic has led to interruptions in care, with a significant impact on the health of patients with chronic conditions or with advanced age, including breast cancer patients [18]. Therefore, it is imperative to adapt to the digital age and have innovative clinical-care information systems that, through e-health strategies, promote prevention, improve quality of life of patients, and provide individualized care to cancer patients and long-term cancer survivors [19]. Thus, information technology is a promising resource that can improve aspects, such as distance, time, and cost barriers [20], in addition to being a great advantage for reaching many patients at any time and place.

The application of information and communication technologies (ICT) in health, also known as digital health, telehealth, or e-health (used interchangeably throughout this paper), is growing at an accelerated rate. Numerous digital interventions have been carried out, as reflected in a systematic review on the subject [21]. Although there is little evidence on the benefits of these interventions for cancer survivors [22], the interventions have shown efficacy in improving patients’ psychological outlook, quality of life, and self-efficacy [21,22,23]. Considering the demonstrated effectiveness of personalized digital interventions in the acquisition of healthy habits and improvement in the quality of life, such interventions have the potential to reach a large number of users as a complement to usual health care. As a response to the health needs of a growing population, such as LS-BC in primary care consultations, it seems appropriate to propose a personalized digital intervention through the use of artificial intelligence to improve the quality of life of this population.

Therefore, the aim of this study is to evaluate the effectiveness of a web-based personalized intervention based on artificial intelligence instead of usual primary health care to improve the quality of life of long-term survivors of breast cancer (>5 years free of disease) and self-efficacy for the management of late sequelae of cancer.

This study is based on the conceptual model of quality of life in cancer survivors by Ferrell, Dow & Grant (1995) [24]. This model was developed at the City of Hope National Medical Centre in Duarte, California, and is one of the most popular in cancer survivors. The model is composed of the four domains of quality of life incorporating physical, psychological, social, and spiritual well-being [24]. Within the model, self-efficacy is instrumental for the management of cancer sequelae in cancer survivors after the medical, functional, and psychosocial consequences of cancer and its treatment.

## 2. Materials and Methods

### 2.1. Research Design

A randomized controlled trial will be conducted to respond to the following hypothesis: a personalized web-based intervention based on the prevention and management of late effects of cancer treatment will be more effective in improving quality of life of long-term breast cancer survivors and self-efficacy for the management of late sequelae of cancer by primary care providers in long-term breast cancer survivors than conventional primary health care.

Participating subjects will be randomly assigned to the 2 treatment groups: the intervention (the CUMACA-M programme) and control groups (standard care in nursing consultation). The name of CUMACA-M refers to care beyond breast cancer in its original Spanish name (CUidados Más Allá del Cáncer-Mama).

### 2.2. Methodological Framework

The study will be framed in the methodological framework of the Medical Research Council (MRC) for the development and evaluation of complex interventions [25,26]. This process has several phases, although they do not have to follow a linear sequence: Phase I modeling/design; Phase II or exploratory trial to evaluate the acceptability and feasibility of the intervention; Phase III or randomized controlled trial; and Phase IV or implementation into clinical practice. The latest update of the MRC highlights the dynamic relationship between the intervention and its context [26]. It incorporates different perspectives of intervention, efficacy, and effectiveness based on theory or systems, depending on what is already known and the additional evidence that is more useful. Four main phases of the investigation are maintained: development of the intervention or identification, feasibility, evaluation, and implementation. Each phase considers 6 basic elements: How does the intervention interact with its context? What is the underlying programme theory? How can diverse stakeholder perspectives be included in the research? What are the main uncertainties? How can the intervention be refined? Do the costs justify the effects of the intervention? These basic elements can be used to decide whether the research on a complex intervention should move to the next phase, return to a previous phase, repeat a phase, or stop.

How is complex intervention defined according to the MRC? A complex intervention generally contains several components that interact with each other and that entail a significant number of problems for the evaluators, in addition to practical and methodological difficulties. In this study, the web-based personalized programme presented below is based on a complex intervention that contains different interacting components: the type of participants, LS-BC as an emerging population; the type of intervention based on artificial intelligence; the variables analyzed that consist of several dimensions of quality of life (physical, emotional, social, and spiritual); the evaluation of the programme at 4 different times (preintervention, 3 months, 6 months, and 9 months); and the specific context of primary health care. All these components make the intervention of this protocol complex and, therefore, suitable for the MRC framework. In addition, it is a digital health intervention and a web-based tailored intervention, and most web-based interventions are complex interventions [27].

The protocol presented here focuses on Phase III related to the randomized controlled trial (Figure 1, grey colour). Phase I of the intervention is being developed through the review of publications on recommendations and clinical practice guidelines regarding breast cancer survivors, their health care needs once the treatments have been completed, in addition to guidance from a panel of experts including health care professionals from specialized care and PHC (oncologists, cancer nurses, psycho-oncologists, general practitioners, and community nurses), LS-BC and breast cancer patient associations. The result will allow configuration of the content of the intervention. Simultaneously, in this same phase, the digital health intervention will be designed (web and mobile application format). Once this evidence is available, in Phase II of the MRC, the intervention will be piloted with LS-BC (*n* = 20) to evaluate the feasibility of the intervention protocol, to know the usability of the web programme and to detect possible risks, failures, or problems and to solve them before completing the study in Phase III.

In Phase IV, considering the current situation and implementation in Spain of the Comprehensive Care Plan for Long-term Cancer Survivors of the Spanish Society of Medical Oncology [5], the intervention will be negotiated with the competent health authorities of the region for its implementation in the region’s primary care centers. An innovative practice in the provision of health services, which will make it possible to remove barriers due to distance, time, and cost, in addition to reaching many patients simultaneously at any time and place. In turn, this will allow personalized care for long-term cancer survivors.

### 2.3. Settings

The study will be carried out in Navarra, an autonomous community and province in northern Spain, with a total population of 482,916 people. Six primary health centers from different municipalities in northern (country blinded for review) will be selected to participate in the research. If the sample size of long-term cancer survivors is not reached, new primary health centers will be incorporated.

### 2.4. Inclusion and Exclusion Criteria

The subjects will be LS-BC who have completed active treatments and who meet the following inclusion criteria: female over 18 years of age, having been diagnosed with breast cancer, having completed active cancer treatments (chemotherapy and/or radiotherapy) in a period of time greater than 5 years after diagnosis, being free of disease at the time of data collection, and knowing how to use the internet. Exclusion criteria are as follows: women with a diagnosis of cancer other than breast cancer, being in active treatment for recurrence or new cancer, receiving palliative care, or being male. Although almost 1% of breast cancer diagnoses are in men, they will not be included in this study because their needs may be different from those of women, especially in relation to the psychosocial dimension.

### 2.5. Sample Size

For the calculation of the sample size, a primary outcome measure, quality of life (QOL), was selected [28]. The QOL measure used for this study goes from 1 (extremely poor) to 10 (excellent). A Cohen’s d of 0.4 (effect size) was established, taking into account a difference in quality of life of 0.75 and a standard deviation of 1.8. This effect size has been established, taking into account previous studies [29], and is expected to occur over time, after the intervention. For its part, the type I error has been set at 5% and the type II error at 20%. According to these parameters, 91 subjects will be needed in the intervention group (IG) and 91 subjects in the control group (CG). Depending on the proportion of losses that may occur, the sample size will be increased, calculating an adjusted sample size. In the event that the pilot study suggests making modifications in the calculation of the sample size due to a re-estimation of the effect size, the appropriate corrections will be made before beginning the study. In this study, sample size estimation was performed using the Granmo Calculator, available online in several languages (https://www.imim.cat/ofertadeserveis/software-public/granmo/) (accessed on 15 May 2022.).

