### 2.7. Description of the CUMACA-M Intervention

The personalized digital intervention will be designed in web and mobile application format to facilitate access at any time and from any place, regardless of the device used (computer, tablet, or smartphone). As it is a personalized intervention with the use of different algorithms using artificial intelligence, participants will receive information adapted to their personal needs. As mentioned above, the contents will be developed from an exhaustive review of recommendations and clinical practice guidelines for the care of LS-BC and on the main needs of LS-BC (Phase I of the MRC). Subsequently, the content of the intervention will be agreed upon by a panel of multiprofessional experts from PHC and specialized care, as well as an LS-BC and a representative of an association supporting women with breast cancer.

These contents will be configured in different modules according to the areas identified as priority needs of the LS-BC (for example, fatigue module, lymphedema module, work activity module, and fear of recurrence module), and the principles of the educational intervention characteristic of PHC consultations will be followed (feedback methods, risk personalization, increased awareness, active learning, persuasive communication, goal setting, and actions) [30].

The main page of the digital intervention programme will show a personal record and a video on how to use the programme. The intervention will begin with a screening questionnaire that will measure several concepts that impact quality of life, such as fatigue, anxiety, fear of recurrence, or return to work. According to the responses, participants will receive personalized advice by means of artificial intelligence algorithms on which modules deserve more attention. The web application itself will integrate the measurement of outcome variables that will allow evaluation of the effectiveness of the intervention. The effective management of the topics identified for the intervention will ultimately improve the quality of life of the LS-BC.

In Phase II (feasibility and piloting), the pilot of the intervention will be carried out through a pre-experimental pretest–post-test design with a single group that will pilot the intervention and test the usability of the application to identify areas for improvement and introduce timely modifications.

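### Section 2.5 lets a 20-woman pilot with no control group re-estimate the effect size and so reset the sample size, a task that pilot cannot do

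*Protocol article*

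**What the plan says.** Section 2.5 (Sample Size) bases the calculation on quality of life, with "a difference in quality of life of 0.75 and a standard deviation of 1.8", a type I error of 5% and a type II error of 20%. This gives 91 women in each group. The effect size is attributed to previous studies. The section then adds a conditional clause that begins "In the event that the pilot study suggests making modifications in the calculation of the sample size due to a re-estimation of the effect size". Should that happen, the section promises that "the appropriate corrections will be made before beginning the study".

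Two other sections describe the pilot. Section 2.2 (Methodological Framework) says "the intervention will be piloted with LS-BC (*n* = 20) to evaluate the feasibility of the intervention protocol", and adds usability and the detection of problems as aims. Section 2.7 (Description of the CUMACA-M Intervention) makes it a pre-experimental before-and-after design "with a single group that will pilot the intervention and test the usability of the application".

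The trial itself compares two groups over four time points (section 2.10). The control group receives a one-hour nurse consultation, a brochure and brief lifestyle advice (section 2.9).

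**The concern.** The clause in section 2.5 gives the pilot a task that its design in sections 2.2 and 2.7 does not allow, for two separate reasons.

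- **Wrong quantity.** The 0.75 behind 91 per group is a difference between intervention and control. A single group yields only a within-group change. That change combines the programme effect with time, repeat testing, regression to the mean and whatever improvement the control consultation would also have produced. A larger pilot without controls would not cure this.
- **Too little information.** Twenty women cannot fix a mean change closely enough to choose between a much smaller and a much larger trial.

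Power and trial size are at stake. A pilot result that is high, by chance or because of non-specific improvement, could be used to justify a smaller trial with poor power for the difference the sponsor chose. A low result could call for a far larger trial without good reason.

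**Working it through.** **Inputs from the protocol article.** Difference 0.75, SD 1.8, alpha 5%, power 80%, 91 per group (section 2.5); 96 per group planned, as 6 centres × 16 (section 2.6); pilot of 20 (section 2.2) in a single group (section 2.7); QOL-CS test-retest reliability 0.89 (section 2.8).

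**Assumed, because the documents give neither.** The pre-post correlation ρ, taken as 0.3, 0.5, 0.7 and 0.89, with the stated reliability as the most favourable value. The improvement in controls, taken as 0.10, 0.25 and 0.40 points.

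**1. The plan's own figure.** n per group = 2 × (1.960 + 0.842)² × (1.8/0.75)² = 2 × 7.849 × 5.76 = 90.4, rounded up to 91. This matches, with a two-sided test. The two-sample formula reproduces the number, so 0.75 is being used as a between-group difference. Power is 80.3% at 91 per group and 82.3% at 96.

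**2. Precision of the pilot.** SD of change = 1.8 × √(2(1 − ρ)). Half-width of the 95% CI = 2.093 × SD of change / √20. Each limit around a pilot estimate of 0.75 is put back into the formula of step 1, with the SD kept at 1.8.

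| ρ (assumed) | SD of change | Half-width | 95% CI | Implied n per group |
|---|---|---|---|---|
| 0.3 | 2.13 | 1.00 | −0.25 to 1.75 | 17 to no finite n |
| 0.5 | 1.80 | 0.84 | −0.09 to 1.59 | 21 to no finite n |
| 0.7 | 1.39 | 0.65 | 0.10 to 1.40 | 26 to 5355 |
| 0.89 | 0.84 | 0.40 | 0.35 to 1.15 | 39 to 404 |

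The half-width exceeds the target of 0.75 at the two lower correlations and is more than half of it at the highest. The SD of change equals 1.8 only at ρ = 0.5. At any other value, a standardised effect computed on change scores is not on the same scale as 0.75/1.8.

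**3. An ordinary chance result.** Suppose that the true change is 0.75 with no contribution from other sources, and that the pilot lands at its 75th percentile.

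| ρ (assumed) | Pilot estimate | n per group | True power for 0.75/1.8 |
|---|---|---|---|
| 0.3 | 1.07 | 45 | 51% |
| 0.5 | 1.02 | 49 | 54% |
| 0.7 | 0.96 | 56 | 60% |
| 0.89 | 0.88 | 67 | 67% |

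**4. Bias from having no controls.** If controls would also improve by c, the pilot's expected change is 0.75 + c. Using it as the effect gives n = 2 × 7.849 × (1.8/(0.75 + c))².

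| c (assumed) | Pre-post change | n per group | True power for 0.75/1.8 |
|---|---|---|---|
| 0.10 | 0.85 | 71 | 70% |
| 0.25 | 1.00 | 51 | 56% |
| 0.40 | 1.15 | 39 | 45% |

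This loss comes before any sampling error.

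**5. The SD alone.** With 20 women and an observed SD of 1.8, the 95% CI is 1.8 × √(19/32.85) = 1.37 to 1.8 × √(19/8.91) = 2.63. With 0.75 kept fixed, that is 53 to 193 per group.

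**The case against.** The best defence is that Cohen's d has two parts, and that re-estimating it could mean updating only the SD while 0.75 stays. The article does not say that the pilot's mean change will replace 0.75. That reading is possible, but nothing in section 2.5 keeps 0.75 fixed, and an effect size includes the mean difference. Step 5 shows that even the SD-only reading is too imprecise to justify a reduction.

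A second defence is that the full protocol may hold the rules for such a review. Missing detail is indeed no fault in an article. The point here is the stated use of the pilot, which the stated design cannot support whatever the detail.

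Third, the clause is conditional, and any correction comes before the trial begins. This stands and limits the point. A reader might infer that the sponsor plans to shrink the trial, or to move the sample size in either direction. The text says neither. It sets no direction, so a reduction is merely not excluded, and the only directional statement nearby is an increase for losses. A reader might also suspect inflation of type I error. That does not follow, because no trial outcome data exist when the correction would be made.

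**Conclusion.** The point holds, within limits. As written, section 2.5 lets a single-group study of 20 women re-estimate the effect behind a between-group calculation. That study has no control contrast, and over the whole assumed range of correlation it is too imprecise to reset the sample size: at best the implied n runs from 39 to 404 per group. With an assumed control improvement of 0.10 to 0.40 points, using the raw change would give about 71 to 39 per group and true power of about 70% to 45%.

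These sizes are illustrations that rest on the assumed correlation and control change. They are not forecasts. Harm also needs a chain of events: the pilot prompts a change, its mean change is taken as the effect, and the sample size is altered accordingly. The present 91 per group is not in question, since it reproduces and gives 80% power. The wording should be changed before the trial starts, because it puts that power at risk for no gain in information.

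**What to change.** In section 2.5, delete the re-estimation of the effect size and state that 0.75 points remains the target between-group difference. Say what the pilot will inform:

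- usability and questionnaire completion;
- the loss rate, which the section's own adjustment for losses needs and for which it gives no figure;
- at most, a check on the quality-of-life SD that may raise the sample size but not lower it, given how imprecise an SD from 20 women is.

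The cost is about one sentence of wording. The sponsor gives up the option to shrink the trial on pilot results. A chance high SD could also make the trial larger than it needs to be, which is the price of allowing increases only.
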